#### 2. Principles for Dose Adjustment and Interruption

When a grade 3/4 hematological/non-hematological AE occurs, the researcher should judge its relation to targeted agent/chemotherapy drugs: if the toxicity is related to the targeted agent, reduce the dose of apatinib to 250 mg qd; if the toxicity is related to chemotherapy drugs, reduce the dose or discontinue the treatment of Tigio or oxaliplatin. If the researcher cannot determine the relation between the toxicity and the drugs, it is recommended to discontinue apatinib first and observe for 24 hours. If the toxicity does not resolved, discontinue the chemotherapy drugs.

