#### 1. General Considerations for Dose Adjustment

- For AEs present at baseline, the dose can be adjusted according to the change in grades. For example, if grade 1 weakness at baseline progresses to grade 2 during treatment, the dose can be adjusted as the presence of a grade 1 toxicity.
- There is no need to reduce the dose or discontinue the treatment with the presence of the toxicities which are unlikely to develop into severe events (such as hair loss, appetite changes, etc.) occur. Additionally, there is no need to reduce the dose or discontinue the treatment with the presence of anemia (non-hemolytic) because it can be improved by transfusion.
- When different grades of toxicities occur simultaneously, dose reduction should be taken according to the most severe of them.
- During treatment, if all study drugs need to be delayed or discontinued for more than six weeks, the patient will withdraw from the study. If only one drug is discontinued, the study still proceeds.
- If a patient develop a grade 3 or higher non-hematological AE, it can be discussed with the sponsor whether to reduce the dose or not.

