### 3. Apatinib

#### 3.1 Dose

The initial dose is 500 mg, qd; this dose can be reduced to 250 mg, qd, or 250 mg, qod. Subsequent dose reduction is not permitted.

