#### 3.2 Principles for Dose Adjustment and Interruption

- Dose reductions are allowed in the presence of grade 3 treatment-related toxicities.
- Among non-hematological toxicities, there is no need to reduce the dose or discontinue the treatment in the presence of manageable nausea, vomiting, hair loss, fever with a defined cause (such as infection or tumor), and grade 3/4 elevated alkaline phosphatase (AKP).
- Dose reductions are allowed up to twice. Treatment interruption is allowed for no more than 14 days (cumulatively) and no more than two times in each cycle. Dose re-escalation is not permitted.
- Treatment interruption is first performed during each cycle. Then dose reduction can be performed when the subject is still intolerant.
- Special AEs: Once hypertension crisis, cerebral hemorrhage, grade 2 or higher pulmonary hemorrhage, grade 3 or higher other bleeding, arterial thrombosis, grade 4 venous thrombosis, leukoencephalopathy syndrome, or gastrointestinal perforation occurs, immediately discontinue the treatment and perform active symptomatic treatment; the subject then withdraw from the study.

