#### Principles for Dose Adjustment of Apatinib

| Classification | Grade | Regulations for Dose Adjustment                                                                                                                                                                               |
|----------------|-------|---------------------------------------------------------------------------------------------------------------------------------------------------------------------------------------------------------------|
| Hematologic    | 1-2   | Maintain the original dose                                                                                                                                                                                    |
|                | 3     | Discontinue the treatment until the toxicity $\leq$ grade 2, then continue the treatment at the original dose. If a grade 3 or higher toxicity recurs, continue the treatment after one-level dose reduction. |
|                | 4     | Discontinue the treatment until the toxicity $\leq$ grade 2, then continue the treatment after one-level dose reduction.                                                                                      |
| Nonhematologic | 1-2   | Maintain the original dose                                                                                                                                                                                    |
|                | 3     | Discontinue the treatment until the toxicity $\leq$ grade 1, then continue the treatment at the original dose. If a grade 3 or higher toxicity recurs, continue the treatment after one-level dose reduction. |

|  |   |                                                                                                                          |
|--|---|--------------------------------------------------------------------------------------------------------------------------|
|  | 4 | Discontinue the treatment until the toxicity $\leq$ grade 1, then continue the treatment after one-level dose reduction. |
|--|---|--------------------------------------------------------------------------------------------------------------------------|

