#### 4. Tigio / oxaliplatin

Dose reductions are allowed in the presence of grade 3 hematologic or grade 2 nonhematologic toxicities. When different toxicities occur simultaneously, dose reduction or interruption should be taken according to the most severe of them.

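### Appendix 5 gives incompatible apatinib instructions after a first grade 3 toxicity attributed to apatinib at 500 mg daily, and does not say which prevails

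*Protocol*

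**What the plan says.** Four places in Appendix 5 of the protocol bear on apatinib after a grade 3 toxicity.

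- Item 2, Principles for Dose Adjustment and Interruption, covers both toxicity classes and both severe grades: "When a grade 3/4 hematological/non-hematological AE occurs, the researcher should judge its relation to targeted agent/chemotherapy drugs". Where the event is attributed to apatinib, the action is: "if the toxicity is related to the targeted agent, reduce the dose of apatinib to 250 mg qd". It mentions no interruption for such an event, no return to the previous dose, and no difference between a first and a repeated event.
- Item 3.2, which concerns apatinib alone, is permissive on reduction: "Dose reductions are allowed in the presence of grade 3 treatment-related toxicities". It also fixes an order of actions: "Treatment interruption is first performed during each cycle", with reduction available afterwards if the patient still cannot tolerate the drug. It allows two reductions and forbids raising a reduced dose again.
- The apatinib table that follows has a grade 3 row for each toxicity class. Both stop the drug until recovery (to grade 2 or lower if haematological, grade 1 or lower if not), "then continue the treatment at the original dose. If a grade 3 or higher toxicity recurs, continue the treatment after one-level dose reduction".
- Item 1, General Considerations, says that for non-haematological events of grade 3 or above the question of reducing may be taken up with the sponsor.

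Item 3.1 sets the dose levels: "The initial dose is 500 mg, qd; this dose can be reduced to 250 mg, qd, or 250 mg, qod". Item 2 does not refer to item 3 or to the table, and no sentence gives one text precedence.

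**The concern.** For one and the same event, one instruction lowers the dose and another restores it. A site that works from item 2 and a site that works from the table will treat identical patients differently, and neither deviates from the protocol. The choice is hard to undo, because a reduced dose may not be raised and each reduction uses one of the two allowed.

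Patient safety comes first. Drug safety is also a listed outcome (synopsis; Section 3.5.2). In a multicentre, single-arm study of 50 patients, toxicity rates, counts of dose reductions and apatinib exposure would partly reflect which page each site had read. Finally, Section 3.2.3 rejects patients who do not take the drugs as the protocol prescribes, and the per-protocol set in Section 6.2 requires compliance with the protocol. With two prescribed doses for one event, neither criterion has a fixed reference.

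**Working it through.** The protocol states no figure to reproduce, so the check follows each rule for a patient on 500 mg daily whose toxicity is attributed to apatinib.

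| Event | Item 2 | Apatinib table | Resulting dose |
|---|---|---|---|
| First grade 3 | 250 mg daily | Interrupt until recovery, then 500 mg daily | Conflict |
| Recurrent grade 3, still on 500 mg | 250 mg daily | One level down: 250 mg daily | Agrees |
| First grade 4 | 250 mg daily | Interrupt until recovery, then one level down: 250 mg daily | Agrees; only the interruption differs |

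Item 3.2 sides with the table on the order of actions. Item 1 adds a third route for a non-haematological event: a case-by-case discussion whose outcome is open. The direct contradiction is therefore confined to the first row.

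A side effect appears lower down the scale. For a patient already on 250 mg daily, item 2 names the dose already being taken, whereas one level down under item 3.1 and the table is 250 mg on alternate days.

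**Size per patient.** The daily doses after the event are 500 mg and 250 mg, a ratio of 500/250 = 2. Over a full 21-day cycle that is 21 × 500 = 10,500 mg against 21 × 250 = 5,250 mg. During the table's interruption the order is reversed: no drug under the table, 250 mg daily under item 2 as written. The gap closes if the patient following the table has a recurrence and is reduced.

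**Duration.** Section 4.2 plans 2 to 5 preoperative cycles and stops apatinib in the last one. Read as omission for that whole cycle, this leaves 1 to 4 preoperative cycles with apatinib. Section 4.4 plans 6 postoperative cycles with apatinib, so 7 to 10 in all. If the event falls in cycle 1, the full apatinib cycles still to come are:

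- before surgery: 1 − 1 = 0 to 4 − 1 = 3;
- with the adjuvant cycles added: 0 + 6 = 6 to 3 + 6 = 9.

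Which range applies is not settled. Appendix 5 opens by speaking of toxicity in preoperative treatment, and Section 4.4 states 500 mg again without saying whether an earlier reduction carries over.

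**Share of patients.** Those affected have a first grade 3 event attributed to apatinib that falls outside the exceptions in items 1 and 3.2 and outside the special adverse events that end participation. The protocol gives no rate for this. Each such patient is 1/50 = 2% of the planned sample.

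**The case against.** The best defence is that item 2 is a general principle which sorts events by the responsible drug, and item 3 with its table is the drug-specific detail. Items 3.2 and the table do fit together on that reading. But the protocol does not say so, and item 2 is itself specific: it names apatinib and a milligram dose. Reducing the dose and resuming at the previous dose cannot both be done after the same event.

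It is also fair to say that a single-arm trial has no between-arm bias to fear, that full-analysis-set membership needs only one cycle of neoadjuvant treatment, that efficacy is analysed in both sets, and that reasons for dose changes go into the CRF, so differing practice could be seen afterwards. All of this stands. It limits the analytic damage but does not remove the conflict in dosing.

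A reader might infer two further contradictions that the text does not support.

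- *Anaemia.* Item 1 says non-haemolytic anaemia does not require reduction or stopping, and the haematological rows of the table do not repeat this. It reads as a general exception, and a table that omits an exception does not contradict it.
- *Chemotherapy.* Item 4 says "Dose reductions are allowed in the presence of grade 3 hematologic or grade 2 nonhematologic toxicities", while item 2 acts at grade 3/4. A permission at a lower grade and a direction at a higher grade can both be followed.

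**Conclusion.** The contradiction is real and must be fixed, for one event: a first grade 3 toxicity attributed to apatinib at 500 mg daily. Following the text as written gives daily doses that differ two-fold, and the lower one may not be reversed. For a first grade 4 or a recurrent grade 3 event at 500 mg the resulting dose agrees.

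Three larger claims may suggest themselves, and the protocol does not carry them.

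- The share affected is not the whole grade 3 rate. Events attributed to chemotherapy or to no identifiable drug have their own rules in item 2, and the listed exceptions and special events also fall outside.
- The exposure at stake is not 5 + 6 = 11 cycles, because apatinib stops in the last preoperative cycle. Whether a reduction persists into the adjuvant period is unstated.
- Wrongful exclusion from the per-protocol set is a possibility, not an established consequence, since each action is one that the protocol prescribes. What can be said is that the reference for compliance is undefined. Full-analysis-set membership is unaffected.

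The conclusion rests on the wording of Appendix 5 alone and needs no assumption about event rates.

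**What to change.** The sponsor and investigators should reconcile items 1, 2 and 3.2 of Appendix 5 and the apatinib table into one rule for apatinib, set out by toxicity class, grade, and first or recurrent event. The reconciled text should:

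- say which text prevails if any overlap remains;
- say where discussion with the sponsor fits;
- say how the exceptions in items 1 and 3.2 relate to the table;
- say whether Appendix 5 governs the adjuvant cycles.

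The content of each of these is a decision for the clinical team, and no view is taken here on which instruction is right. Dosing compliance under Section 3.2.3 and for the per-protocol set should then be judged against the reconciled text.

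The cost is an amendment to Appendix 5, its submission to the ethics committees, which Section 9.3 requires, and a notice to sites. Sample size, endpoints and visit schedule do not change. If patients have already been treated, the CRF entries on dose changes can show which instruction was followed after each such event, and these can be listed by site.

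### For a first apatinib-related grade 3 event at 500 mg qd, Appendix 5 orders both a reduction to 250 mg qd and a return to the original dose, with no rule of precedence

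*Protocol*

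**What the plan says.** All the relevant text is in Appendix 5 of the protocol.

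- **Section 3.1** sets the dose levels: "The initial dose is 500 mg, qd; this dose can be reduced to 250 mg, qd, or 250 mg, qod". There is no level below these.
- **Section 2** opens with "When a grade 3/4 hematological/non-hematological AE occurs, the researcher should judge its relation to targeted agent/chemotherapy drugs" and continues "if the toxicity is related to the targeted agent, reduce the dose of apatinib to 250 mg qd". It does not separate grade 3 from grade 4 or a first event from a repeat. Where the event is attributed to apatinib, it has no step for interrupting and resuming.
- **The apatinib table** treats grade 3 the same way for hematologic and nonhematologic toxicity, apart from the recovery threshold. After an interruption it says "then continue the treatment at the original dose. If a grade 3 or higher toxicity recurs, continue the treatment after one-level dose reduction". For grade 4 it says, after recovery, "then continue the treatment after one-level dose reduction".
- **Section 3.2** gives a sequence: "Treatment interruption is first performed during each cycle. Then dose reduction can be performed when the subject is still intolerant". It permits reductions for related grade 3 toxicity without ordering them, caps reductions at two, and adds "Dose re-escalation is not permitted".
- **Section 1** leaves the reduction for non-hematological events of grade 3 or higher open to discussion with the sponsor.

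No passage refers to another as controlling.

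**The concern.** Section 2 gives a complete order: drug, trigger and resulting dose. The table also gives a complete order for the same trigger, and the two end at different doses. An investigator who stops at section 2 and one who goes on to the table both follow the protocol.

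Three things are at stake within the plan itself.

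- **Patient safety.** The instructions after a severe toxicity of the drug under test conflict.
- **Safety outcomes.** Drug safety is a secondary outcome (section 3.5.2). Rates of recurrence and of dose reduction will partly reflect which passage was followed.
- **Analysis sets.** The per-protocol set requires compliance with the protocol (section 6.2, Definitions of Analysis Sets), and section 3.2.3 rejects patients not dosed as prescribed. The same patient is compliant under one passage and a deviator under the other.

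Section 2 also uses up one of the two permitted reductions at the first event, and the table does not. This matters because intolerable toxicity after dose reductions is a reason to stop treatment (section 3.2.4).

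**Working it through.** The plan states no exposure figure on this point, so there is none to reproduce. The check sets the rules side by side and then does the dose arithmetic.

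**Step 1: the rules by case**

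| Case (event related to apatinib) | Section 2 | Apatinib table | Same dose? |
|---|---|---|---|
| First grade 3, on 500 mg qd | 250 mg qd | interrupt, then 500 mg qd | No |
| Grade 4, on 500 mg qd | 250 mg qd | interrupt, then one level down = 250 mg qd | Yes, but section 2 omits the interruption |
| Repeat grade 3, or grade 4, on 250 mg qd | 250 mg qd (read literally, no further step) | interrupt, then one level down = 250 mg qod | No, on a literal reading |

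**Step 2: events outside the conflict**

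Section 1 exempts toxicities unlikely to become severe and non-hemolytic anemia. Section 3.2 exempts manageable nausea and vomiting, hair loss, fever of known cause and grade 3/4 alkaline phosphatase elevation. The special adverse events in section 3.2 end treatment. Hypertension, hand-foot syndrome and proteinuria, which section 3.5.2 names as drug-related events, are on neither exempt list; only hypertensive crisis is handled separately, as a special event.

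**Step 3: dose after recovery**

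Inputs: 500 mg qd and 250 mg qd (Appendix 5, section 3.1); 21 apatinib days per cycle (section 3.3.2).

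- Daily dose ratio: 500 / 250 = 2.0.
- Full cycle after recovery: 500 × 21 = 10,500 mg against 250 × 21 = 5,250 mg.
- Patient already on 250 mg qd: 5,250 mg against 250 × 11 = 2,750 mg per cycle on alternate days starting on day 1.

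**Step 4: cumulative dose**

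Let D be total apatinib days, e the days dosed before the event and w the days interrupted, with no later event.

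- Table: 500e + 500(D − e − w)
- Section 2, without interruption: 500e + 250(D − e)

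The values of e and w are assumptions. Section 3.2 allows at most 14 interrupted days per cycle. Section 4.2 gives 2 to 5 preoperative cycles with apatinib omitted from the last, so 1 to 4 apatinib cycles before surgery; section 4.4 adds 6 after it, for at most 10.

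| Apatinib cycles | e | w | Table (mg) | Section 2 (mg) | Ratio |
|---|---|---|---|---|---|
| 4 (D = 84) | 7 | 7 | 3,500 + 500 × 70 = 38,500 | 3,500 + 250 × 77 = 22,750 | 1.69 |
| 10 (D = 210) | 7 | 7 | 3,500 + 500 × 196 = 101,500 | 3,500 + 250 × 203 = 54,250 | 1.87 |
| 1 (D = 21) | 7 | 14 | 3,500 + 0 = 3,500 | 3,500 + 250 × 14 = 7,000 | 0.50 |

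The cumulative ratio cannot exceed 2 in the table's favour and is usually lower. Within the cycle of the event it can reverse, because the table interrupts treatment and section 2 does not.

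**The case against.** The best defence is that section 2 is a general attribution rule across three drugs, while section 3 and its table are specific to apatinib, so a sensible site would follow the table. Section 3.2 agrees with the table on sequence, section 1 offers a route to the sponsor for non-hematological events, and reasons for dose changes go into the CRF, so actual dosing can be described afterwards. That is a fair reading, but the protocol does not state it. Section 2 names apatinib and an exact dose, the discussion with the sponsor is optional and does not cover hematological events, and recording a dose does not settle which dose was required.

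Two further replies carry weight. The reduction in section 2 can be read as the first step down from 500 mg qd, with section 3.1 supplying the second; the third row of the comparison is therefore a literal-reading problem, weaker than the first. A reader might also take the table's original dose to mean 500 mg even for a patient already reduced, but the ban on re-escalation in section 3.2 excludes that reading. The term needs clarifying and is not a second contradiction.

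Some stronger inferences are not supported. A reader might turn this into a number of affected patients, but the protocol gives no rate of related grade 3 events, and a combined grade 3/4 rate would include grade 4 events at the starting dose, where the doses agree. A reader might expect a shift in the R0 rate, but the protocol gives no relation between apatinib dose and R0. A reader might expect differences between sites; the trial is multicenter, but the variation could equally be between investigators or patients.

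**Conclusion.** The contradiction is real and must be fixed. It is firm for one case: a first apatinib-related grade 3 event, hematologic or nonhematologic, at 500 mg qd, outside the exempt and treatment-ending events. In that case the daily dose after recovery differs by a factor of exactly two, and the gap lasts until a further reduction because re-escalation is barred. The cumulative ratios of 1.69 and 1.87 illustrate the size under the assumed timing and interruption; they are not estimates for this trial.

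The importance of the point rests on conflicting instructions after a severe toxicity and on unclear per-protocol membership. It does not rest on a patient count or on any effect on the primary endpoint. Which rule is clinically right is not a question these documents answer.

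**What to change.** Reconcile Appendix 5, sections 1, 2 and 3.2 and the apatinib table into a single apatinib rule, laid out by toxicity grade, first or repeat event, and current dose level. Let section 2 keep the attribution step and refer to that rule for the action. Say how the optional discussion with the sponsor in section 1 fits in, and whether interruption applies wherever section 2 now omits it. Define the original dose for a patient already reduced, consistently with the re-escalation ban. The sponsor's clinical team must decide which rule stands.

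If any patient was treated before the amendment, state which text governs protocol compliance for the per-protocol set in those cases. The cost is a wording amendment with the usual ethics submission; no extra patients, visits or procedures are needed.

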### 3. Apatinib

#### 3.1 Dose

The initial dose is 500 mg, qd; this dose can be reduced to 250 mg, qd, or 250 mg, qod. Subsequent dose reduction is not permitted.

#### 3.2 Principles for Dose Adjustment and Interruption

- Dose reductions are allowed in the presence of grade 3 treatment-related toxicities.
- Among non-hematological toxicities, there is no need to reduce the dose or discontinue the treatment in the presence of manageable nausea, vomiting, hair loss, fever with a defined cause (such as infection or tumor), and grade 3/4 elevated alkaline phosphatase (AKP).
- Dose reductions are allowed up to twice. Treatment interruption is allowed for no more than 14 days (cumulatively) and no more than two times in each cycle. Dose re-escalation is not permitted.
- Treatment interruption is first performed during each cycle. Then dose reduction can be performed when the subject is still intolerant.
- Special AEs: Once hypertension crisis, cerebral hemorrhage, grade 2 or higher pulmonary hemorrhage, grade 3 or higher other bleeding, arterial thrombosis, grade 4 venous thrombosis, leukoencephalopathy syndrome, or gastrointestinal perforation occurs, immediately discontinue the treatment and perform active symptomatic treatment; the subject then withdraw from the study.

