### 3.4 Research Flow

Start Date: The date on which the written informed consent is signed

End Date: The last day of the post-treatment period (eg, 30 days after the last drug administration).

The expected treatment duration of this study is 36 months, including 24-month enrollment period. Each participants will be followed up from the Start Date to the End Date, and then for at least 5 years.

If some participant receives a new anti-cancer therapy, monitoring of AEs will be terminated at the beginning of this therapy.

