#### **4.3 Preoperative evaluation and surgical period**

After completing neoadjuvant treatment, peripheral blood routine, blood biochemistry, stool routine, urine routine, 12-lead electrocardiograms, tumor markers, and coagulation function should be performed to evaluate the efficacy as well as the patients' physical condition. Without clear surgical contraindications and with the patients' consent, surgery will be performed 2–4 weeks later. If disease progresses, radiochemotherapy or salvage surgery is recommended.

- Record the results of peripheral blood routine, blood biochemistry, stool routine, urine routine, 12-lead electrocardiograms, tumor markers, and coagulation tests which are performed 7 days before and after the surgery;

- Retain pathological tissue specimens after surgery;
- Record the reasons for not surgery;
- Record operation time, blood loss, and intraoperative complications (e.g. major bleeding);
- Record postoperative complications and management;
- Record pathological type, number of lymph nodes harvested and metastasis;
- Record postoperative hospital days.

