#### 4.5 Follow-up period

After the last drug administration, patients enter follow-up period. All patients are followed up with every 3 months during the first 2 years and then every 6 months beyond the third year. The status of each follow-up should be

recorded in the follow-up table.

Assessment of follow-up period: chest X-ray, whole abdominal CT, peripheral blood routine, tumor markers; gastroscopy is recommended to be performed once a year.

Location and time of tumor recurrence or metastasis and cause of death should be recorded in detail.

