### **5.3 Recording and Reporting of AEs**

When AEs or SAEs occur during the treatment period, the time of occurrence, clinical manifestations, management, outcomes, and their relation to the study drugs should be recorded in the CRF. Patients with abnormal laboratory tests should be followed up until the results return to normal or to pre-treatment levels. Any SAE should be recorded in the specific tables and reported to the sponsor, ethics committees, Department of Safety Supervision of CFDA, and Department of Health Administration within 24 hours.

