## **6.2 Definitions of Analysis Sets**

Full Analysis Set (FAS): included patients who receive at least one cycle of neoadjuvant treatment.

Per-protocol Set (PPS): included patients who comply with the study protocol, have good compliance, do not take prohibited drugs during the treatment, receive surgery, and complete the CRF. Analysis of the efficacy should be performed in both FAS and PPS populations.

Safety Analysis Set (SAS): included patients who receive at least one cycle of neoadjuvant treatment and have safety records.

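### Appendix 5 takes patients out of the study after certain toxicities; read literally this conflicts with follow-up of all patients in 3.4 and 4.5, and R0 or survival data could go uncollected

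*Protocol*

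**What the plan says.** Appendix 5 contains two rules that send a patient out of the study.

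- **Item 3.2 (apatinib), special adverse events:** the site must "immediately discontinue the treatment and perform active symptomatic treatment; the subject then withdraw from the study".
- **Item 1 (general considerations):** "if all study drugs need to be delayed or discontinued for more than six weeks, the patient will withdraw from the study". The next sentence gives the contrast: "If only one drug is discontinued, the study still proceeds".

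The follow-up sections make no exception for these patients.

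- **Section 3.4:** "Each participants will be followed up from the Start Date to the End Date, and then for at least 5 years".
- **Section 4.5:** "After the last drug administration, patients enter follow-up period. All patients are followed up with every 3 months during the first 2 years", with six-monthly visits later. Recurrence and cause of death are recorded.

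The analysis-set definitions in 6.2 also keep such patients, provided they have had one cycle: "Full Analysis Set (FAS): included patients who receive at least one cycle of neoadjuvant treatment". The primary endpoint is the R0 resection rate. Overall and disease-free survival are analysed by Kaplan-Meier.

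**The concern.** Stopping a drug and leaving a study are different things. A patient who stops treatment because of toxicity can still be operated on, can still have R0 status determined, and can still be followed for recurrence and death. A patient who has left the study may have none of this recorded.

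The events in Appendix 5 item 3.2 include gastrointestinal perforation and severe bleeding, after which an operation off the study schedule is plausible. The opening paragraph of Appendix 5 introduces it in terms of toxicity in the preoperative treatment. That is the period in which R0 status is still undetermined.

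The loss would be caused by toxicity, so it could not be presumed unrelated to prognosis. A statistical analysis plan can say how missing outcomes are handled, but it cannot supply outcomes that were never collected.

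**Working it through.** **1. Do the texts conflict?** The protocol gives no figure to reproduce here, so the first step is to compare instructions.

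| Place | What happens to the patient |
|---|---|
| Appendix 5, item 3.2 | Treatment stops, then the patient leaves the study |
| Appendix 5, item 1 | Patient leaves the study if all drugs are off for more than six weeks |
| 3.2.4 | Toxicity is a reason for stopping treatment; leaving the study is not mentioned |
| 3.4 | Each participant is followed for at least 5 years after the End Date |
| 4.5 | Follow-up starts after the last drug, for all patients |

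On the literal reading, a site cannot obey both the first two rows and the last two. Two other places favour that reading. Section 3.2.4 has separate wording for stopping treatment only, and 9.6 uses the same verb for a researcher who leaves the study altogether.

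**2. Do other sections secure the data?** Only in part.

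- Section 4.3 tells sites to "Record the reasons for not surgery". An unoperated patient can therefore be identified as not R0. The list in 4.3 does not name resection status, and it does not say that it applies to withdrawn patients.
- Section 5.3 covers events on treatment: "When AEs or SAEs occur during the treatment period, the time of occurrence, clinical manifestations, management, outcomes" and drug relation go into the case report form. An early fatal event would be captured. A later operation or a late death would not be.
- Section 6.1 ends data collection 30 days after the last drug. Six weeks is 42 days, so when the six-week rule applies that window has already closed.

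The R0 gap is therefore a patient withdrawn before surgery and operated on later with no record kept.

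**3. Size for R0.** Input: n = 50 (synopsis, sample size). The number k of Full Analysis Set patients with unknown R0 status is an assumption. The part of the rate left open is k/50.

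- k = 1: 1/50 = 2 points
- k = 3: 3/50 = 6 points
- k = 5: 5/50 = 10 points

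For example, with 5 unknown and an assumed 36 R0 resections among the other 45, the rate lies anywhere from 36/50 = 72.0% to 41/50 = 82.0%.

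**4. Size for survival.** Suppose k of the 50 are censored before any event and nobody else is censored up to the time point. Let S be survival in the others and Sw survival in the withdrawn. The Kaplan-Meier estimate is then S, and the true value is [(50 − k)S + k·Sw]/50. The excess is (k/50)(S − Sw). All of k, S and Sw are assumptions.

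| k | S | Sw | Excess (points) |
|---|---|---|---|
| 1 | 70% | 0% | 1.4 |
| 3 | 70% | 0% | 4.2 |
| 5 | 70% | 0% | 7.0 |
| 3 | 70% | 30% | 2.4 |
| 3 | 70% | 70% | 0 |
| 3 | 50% | 0% | 3.0 |
| 3 | 90% | 0% | 5.4 |

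Check by direct count: 3 are censored first and 33 of the other 47 are alive. The estimate is 33/47 = 70.2%. The true value is 33/50 = 66.0% if all three died (excess 4.2 points) and 36/50 = 72.0% if all three lived (shortfall 1.8 points). The sign depends on how the withdrawn patients fare.

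**The case against.** The best defence is context. Item 3.2 sits in the apatinib part of Appendix 5, and the table after it uses discontinuation for apatinib alone. Item 1 says that stopping one drug does not end the study. After a perforation, stopping only apatinib would leave S-1 and oxaliplatin running, so the second step may simply mean ending the whole regimen. On that reading both steps do work and nothing conflicts with 3.4 or 4.5. Those sections are stated without exception, and an appendix on dose changes is weak ground for overriding them. This stands as a possible reading, but nothing in the text selects it, and each site would have to choose.

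Three further points stand and limit the concern.

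- **Scope.** Appendix 5 is introduced for preoperative toxicity. Its effect on withdrawals during adjuvant treatment is less certain, and those could not affect R0 in any case.
- **Separate issues.** The 30-day limit in 6.1 and the missing resection status in 4.3 concern every patient. The withdrawal wording does not cause them; they only mean that it is not offset elsewhere.
- **Extreme inputs.** The largest survival figures assume that every withdrawn patient dies after being censored. Deaths from the event itself would be recorded as serious adverse events under 5.3.

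A reader might infer that the protocol orders data collection to stop, so that endpoint data will be lost and the survival curves will be too favourable. The documents do not support that. No section expressly ends collection for these patients, and neither their number nor their prognosis is given.

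**Conclusion.** The point holds as a conflict on the literal reading, which the text leaves unresolved. It is not a demonstrated loss of data. What could go uncollected is R0 status for a patient withdrawn before surgery and operated on later, and survival follow-up for patients withdrawn under either rule, most clearly those withdrawn before surgery.

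For R0, each such patient leaves 2 points of the rate open at n = 50; how many there would be is unknown. For survival, the effect is probably small. It is a few points only if several patients are lost and do much worse than the rest, and an upward direction is assumed rather than shown. The wording is still worth correcting, because the potential loss follows toxicity and cannot be repaired at the analysis stage.

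**What to change.** In Appendix 5, items 1 and 3.2, replace the words that take the patient out of the study with: *permanently discontinue all study treatment, remain in the study, and be followed for surgery, resection (R0) status, recurrence and survival under 4.3 and 4.5 unless consent is withdrawn*. R0 status needs naming because 4.3 does not list it.

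In 6.1, add that surgery, R0 status, recurrence and survival are collected to the end of follow-up in 4.5, so that the 30-day limit does not cut them off.

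How a Full Analysis Set patient without a documented R0 resection is counted can be left to the statistical analysis plan; no change to the primary analysis text is needed for this point.

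The cost is two wording changes and one added sentence. Section 4.5 already plans follow-up visits for all patients, so no visits or patients are added.
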